## Abstract

The utilization of graphic novels in the realm of clinical medicine is an infrequent occurrence. However, there is a burgeoning interest in their application across a spectrum of pathological conditions with the ultimate aim of enhancing patient care. This study is a prospective pilot designed to assess the influence of graphic novels on the stress levels and behavioral responses of patients diagnosed with pancreatic lesions and who are to undergo endoscopic ultrasound-guided fine needle biopsy (EUS-FNB). Patients exhibiting radiological and clinical pancreatic lesions needing biopsy will be evaluated consecutively. The inclusion criteria encompass the presence of a solid pancreatic mass or a partially solid mass in the event of a cystic component. The exclusion criteria include patients with cognitive impairments, those currently on benzodiazepines or other psychotropic medications, and those with a prior diagnosis of cancer. The authors have developed a comic panel comprising a sequence of six vibrant vignettes, which delineate the standard procedure of EUS-FNB to the patient. Following hospital admission, patients who meet the enrolment criteria and consent to participate in the study will be randomly assigned to either the test or the control group. A graphic novel will be distributed to all patients in the test group, who will have the opportunity to peruse it while awaiting the procedure. Subsequent to the EUS-FNB, all enrolled patients will complete the Beck Anxiety Inventory (BAI) and a modified version of the Depression Anxiety Stress Scales-21 (termed mDASS-21 or mASS-14). The BAI, a 21-item self-report inventory, is employed to gauge the severity of anxiety in adults. The other questionnaire is a modified rendition of the DASS-21, which originally comprised 21 items segregated into three subscales (anxiety, stress, and depression) with seven items each. The anxiety subscale measures physiological arousal, situational anxiety, and the subjective experience of the effects of anxiety, while the stress subscale assesses chronic non-specific arousal, difficulty relaxing, nervous tension, irritability, agitation, and impatience.

## Introduction

Endoscopy, specifically endoscopic ultrasound (EUS), alongside laparoscopic surgery, is the principal modality for the diagnosis and treatment of severe and occasionally life-threatening pancreatic disorders. Particularly in the context of pancreatic lesions, diagnostic procedures such as EUS with fine needle biopsy (EUS-FNB) can induce states of fear and anxiety in patients. The apprehension and/or anxiety associated with the biopsy procedure may be disproportionate relative to the actual risks or objective threat (1). Waiting for a biopsy can be fraught with fear (“What if it is cancer?”), given that a cancer diagnosis is arguably one of the most stressful, life-altering events an individual can encounter (2). The term graphic medicine was coined by a consortium of researchers, clinicians, and artists to describe a new subfield of research and practice (3). It can be defined as a form of visual storytelling exploring narratives in healthcare, cancer, healing, and disability (4). Graphic medicine is currently a trending topic in health communication, with messages contained within the storytelling of health communication being increasingly described as “creative” and “compelling” (5). Researchers are also demonstrating growing interest in graphic narratives, which continue to emerge as efficacious communication tools in public health (6, 7). Various authors theorize the role of storytelling with comics in shaping behaviors, as in the case of anxiety reduction. Graphic medicine is considered effective by many practitioners because it provides medical professionals with an innovative approach to information dissemination, which is both rapid and comprehensive (8). Graphic medicine uses sequential (though not always narratively linear) visual storytelling to convey health-related experiences or information (9). The use of comics facilitates soft skills, thereby opening up a space in which care professionals can communicate effectively with patients while they are going through emotionally charged situations. With their combination of images, limited text, and relatively short format, comics provide an easy option for the effective communication of health-related messages (10). Consequently, graphic novels have been applied to several fields, including oncology (11), HIV infection (12), eating disorders (13), and oral cancer (14). To date, there have been no applications in the field of endoscopy, so the aim of the present study is to evaluate, for the first time in the literature, the efficacy of colorful graphic novels in reducing anxiety in adult patients waiting for an endoscopic-guided biopsy for pancreatic lesions.

## Materials and methods

### Study design

This is a prospective pilot study evaluating the influence of graphic novels on the stress levels and behavioral responses of patients diagnosed with pancreatic lesions and who are to undergo EUS-FNB. The study is being conducted at ISMETT (Istituto Mediterraneo per i Trapianti e Terapie ad Alta Specializzazione), IRCCS (Istituto di Ricovero e Cura a Carattere Scientifico) or the Scientific Institute of Hospitalization and Care in collaboration with UPMC Italy (University of Pittsburgh Medical Center, Italy), located in Palermo, Italy. The study adheres to the principles of the Declaration of Helsinki regarding experimentation involving human subjects, and written informed consent will be procured from all enrolled participants. The protocol is under evaluation of the ethical committee with number IRRB/43/23 and it is registered to ClinicalTrials.gov (NCT06268106). The authors will consecutively evaluate all patients with radiological and clinical suspicion of a pancreatic lesion from from May 2024 to October 2024. The inclusion criteria are (1) age ≥ 18 years; (2) pancreatic solid mass or partially solid in the case of a cystic component requiring tissue acquisition; (3) agreement to participate in the study by signing the informed consent form, and the ability to read and understand the informed consent form; and (4) patients not affected by any known psychological disorder. The exclusion criteria are (1) patients with cognitive deficits, such that they cannot adequately complete the questionnaire, and the visually impaired; (2) suspected or obvious pregnancy status in female patients; (3) patients using benzodiazepines or other psychotropic medications; and (4) patients with a previous diagnosis of cancer. Following hospital admission, patients successfully enrolled and consenting to participate in the study will be randomly allocated to the test or control group using dedicated software (Random Allocation Software, version 1.0) (15). Patients randomized to the control group will experience the standard daily routine in case of EUS-FNB of a pancreatic lesion at our institute, including procedure explanation and consent acquisition. Moreover, it will include an initial colloquium with physical examination, during which the physician explains how the day will unfold, addressing any procedure-related and medical care-related questions the patient may have. After the initial explanation of the daily medical routine, the physician will ask the patient to read the informed consent and to sign it, if they agree. The patient then waits in their room until it is their turn to be brought to the endoscopic room for the EUS-FNB. In case of randomization to the test group (**Figure 1**), the graphic novel will be provided to the patients after the initial colloquium, leaving them waiting for the procedure with the graphic novel, allowing them to read it while waiting and to assimilate slower how their day will unfold.

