### Assessing anxiety

After EUS-FNB, all the recruited patients will receive the Beck Anxiety Inventory (BAI) (16) and a modified version of the Depression Anxiety Stress Scales-21 (mDASS-21) (17) (**Figure 1**). Prior to the endoscopic procedures (i.e., EUS-FNB), these questionnaires will be administered anonymously in a mixed paper-pencil and/or QR code mode to be used with a personal mobile phone. A physician, nurse or clinical assistant will be present for questions and clarification. The BAI is a 21-question self-report inventory used to assess anxiety severity in adults older than 17 years. Respondents answer questions about common anxiety symptoms, such as numbness, tingling, sweating unrelated to heat, and fear of catastrophic events. The BAI takes approximately 5 to 10 min to complete. Scores range from 0 (not at all) to 3 (severe), with higher scores indicating more severe anxiety. Standardized cutoffs classify anxiety levels as minimal, mild, moderate, or severe. The other questionnaire is a modified version of the DASS-21, which originally consisted of 21 items divided into three subscales (anxiety, stress, and depression) with seven items each. We focused on the anxiety and stress subscales, so we modified the questionnaire by removing the depression subscale. Specifically, the anxiety subscale assesses physiological arousal, situational anxiety, and subjective experience of the effects of anxiety, while the stress subscale evaluates chronic non-specific arousal, difficulty in relaxing, nervous tension, irritability, agitation, impatience, and overactivity. Each item is rated on a 4-point scale from 0 (did not apply to me at all) to 3 (applied to me very much, or most of the time). The total score for each subscale ranges from 0 to 14 in our modified version, with higher scores indicating higher levels of anxiety and stress. We named this modified version mDASS-21 or mASS-14. The mASS-14 has four cutoff points to classify anxiety and stress levels: normal (0–4), mild (5–8), moderate (9–11), or severe (12–14). Since the DASS-21 is a reliable and valid measure of anxiety and stress symptoms with good internal consistency, test–retest reliability, and discriminant validity, we will evaluate its modified version in our scenario. Both the BAI (**Figure 3**) and mDASS-21 (**Figure 4**) used in this pilot study were in the Italian versions to avoid language barriers.

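### As the article reads, allocation precedes an open-ended colloquium that covers the same ground as the comic; withholding the arm until the colloquium ends would remove an avoidable bias

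*Protocol article*

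**What the plan says.** The protocol article, Study design, places allocation thus: "Following hospital admission, patients successfully enrolled and consenting to participate in the study will be randomly allocated to the test or control group". The next step described is control care: "Patients randomized to the control group will experience the standard daily routine in case of EUS-FNB of a pancreatic lesion at our institute". That routine is said to include the explanation of the procedure and the taking of consent. Of the same routine the article adds that "it will include an initial colloquium with physical examination, during which the physician explains how the day will unfold", with the patient's questions answered as they arise. After the explanation, "the physician will ask the patient to read the informed consent and to sign it, if they agree", and the patient then waits in the room to be called. In the test arm, "the graphic novel will be provided to the patients after the initial colloquium", to be read during that wait.

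On the outcomes, the section Assessing anxiety says: "The BAI is a 21-question self-report inventory used to assess anxiety severity in adults older than 17 years". The modified DASS-21 is likewise rated item by item on a scale from 0 to 3. On how the forms are completed, "these questionnaires will be administered anonymously in a mixed paper-pencil and/or QR code mode to be used with a personal mobile phone", and "A physician, nurse or clinical assistant will be present for questions and clarification".

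The article does not say whether the colloquium follows a script, whether the physician who conducts it knows the arm, or whether the person present at the questionnaires knows it.

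**The concern.** The comparison is standard explanation against standard explanation plus a comic. The colloquium tells the patient how the day will go, and the comic depicts the same routine so that the patient can take it in more slowly. The two act on anxiety by the same route. If the physician knows the arm before speaking, the colloquium can become a co-intervention that differs by arm. A physician might say less to a patient who is about to receive the comic, say more to a control patient to compensate, or be more thorough with test patients out of interest in the study. The first two would shrink the difference between arms and the third would enlarge it.

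The planned between-group tests compare scores as recorded. They cannot separate the effect of the comic from that of an unequal colloquium, because the length and content of the colloquium are not among the data listed under Data collection. The Discussion says the results could guide the design of later trials, so a shift in either direction would be carried forward.

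The second route is smaller. A member of staff who knows the arm and helps with an anxiety questionnaire may influence the answers, by being there or by the way an item is clarified.

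**Working it through.** The article gives no sample size, effect size or standard deviation, so there is no figure to reproduce. The check is mainly one of sequence.

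**Order of steps**

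1. Study design allocates patients who are admitted, enrolled and consenting. The Abstract gives the same order: admission, eligibility and consent, assignment, then the comic for the test arm.
2. The control routine is then described for patients already called randomised, and that routine contains the explanation, the consent and the colloquium. Read in order, allocation comes first.
3. One sentence could point the other way. The patient signs a consent after the explanation. If this is consent to the study, allocation of consenting patients must follow the colloquium.
4. However, the article lists the taking of consent as part of the institute's standard routine for the biopsy, next to the explanation of the procedure. That fits consent to the procedure better. Allocation before the colloquium is therefore the better-supported reading, though it is not stated outright.

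**When the arm has to be known**

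The first action that differs by arm is handing over the comic, which happens after the colloquium. Everything before that is meant to be the same in both arms, so knowing the arm earlier serves no purpose in the study.

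**Staff at the questionnaires**

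The article has a physician, nurse or clinical assistant present and does not say whether that person knows the arm. Against this, completion is anonymous and may be on the patient's own phone. The risk is open but already reduced.

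**Illustration of scale (all inputs assumed)**

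Suppose the comic has no effect and staff behaviour shifts one arm by b standard deviations. For a two-sided 5% z-test with n patients per arm, let d = b / √(2/n). The chance of a significant result is

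1 − Φ(1.96 − d) + Φ(−1.96 − d).

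For n = 50 and b = 0.2, √(2/50) = 0.2 and d = 1, which gives 1 − Φ(0.96) + Φ(−2.96) = 0.170. Over a range:

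| n per arm | b = 0 | b = 0.1 | b = 0.2 | b = 0.3 |
|---|---|---|---|---|
| 20 | 5.0% | 6.2% | 9.7% | 15.8% |
| 30 | 5.0% | 6.7% | 12.1% | 21.3% |
| 50 | 5.0% | 7.9% | 17.0% | 32.3% |
| 100 | 5.0% | 10.9% | 29.3% | 56.4% |

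The test is two-sided, so the table is the same whichever arm is favoured. It shows only how a shift of a given size would act. It is no evidence that such a shift will occur.

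**The case against.** The strongest objection is that the article never says allocation comes before the colloquium. The sentences on the control arm may describe care by arm and not a timeline, the consent signed after the explanation may be the study consent, and Figure 1, which gives the study overview, is not shown in the text available here and may settle the order. This stands to the extent that the order is an inference. It does not dispose of the point: if the investigators already intend allocation after the colloquium, the same sentence added to Study design makes that clear and changes nothing in practice.

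A second objection is that masking of staff and a script for the colloquium are details an article may leave to the full protocol. That is fair, and their absence is not the point here. The point is the sequence that the article does set out, which exposes the colloquium to knowledge of the arm without need.

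A reader might go further and infer that staff who know the arm sit with patients while they rate their anxiety, and that this could by itself create the difference. The documents do not support that. They say only that someone is available for questions, they do not say that this person knows the arm or handed out the comic, and they specify anonymous completion. A reader might also infer that any bias would favour the comic. For the colloquium the direction is unknown, since compensating explanation to controls would work against it.

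Finally, patients cannot be masked to receiving a comic, so expectation will affect self-report whatever is done. This is correct and limits what the change achieves, but it is no reason to leave a second, avoidable source of bias in place.

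**Conclusion.** The point holds in a limited form. On the natural reading of Study design, allocation precedes an open-ended physician explanation that overlaps with the intervention, and the outcomes are subjective. That leaves room for a co-intervention that differs by arm, in either direction, and the design does not need it. The conclusion rests on two assumptions: that the consent within the biopsy routine is consent to the procedure, and that an arm once allocated is not withheld from the physician.

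The size of any bias cannot be derived from the documents. On assumed values only, a shift of 0.2 SD would raise a 5% false-positive rate to between 9.7% (20 per arm) and 29.3% (100 per arm). The change is worth making because it costs very little, not because a large bias has been shown. The presence of staff at the questionnaires is a secondary matter, already partly dealt with by anonymous completion.

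**What to change.** In Study design, state that the allocation is generated, or at least disclosed, only after the colloquium and procedure consent are complete. Both arms then receive the same colloquium from a physician who does not know the arm. Say also which consent is signed after the explanation, so that the order of study consent, procedure consent and allocation is explicit, and make sure Figure 1 agrees. The cost is a change in the order of steps: someone must obtain the allocation between the end of the colloquium and the wait. No staff are added, and care in either arm does not change.

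In Assessing anxiety, keep the anonymous paper or QR completion and add one instruction: patients complete and submit the form on their own, and help is given on request, where existing staffing allows, by someone who did not hand out the comic. When the results are reported, acknowledge that patients knew whether they had received the comic, because neither step removes that influence.

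### Patients are randomised before what is most naturally the procedure consent, and if the questionnaires follow EUS-FNB, as two of three timing statements say, a randomised patient without a biopsy has no outcome

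*Protocol article*

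**What the plan says.** **Eligibility and allocation (Study design).** The lesion criterion is "pancreatic solid mass or partially solid in the case of a cystic component requiring tissue acquisition". A separate criterion is "agreement to participate in the study by signing the informed consent form". After admission, "patients successfully enrolled and consenting to participate in the study will be randomly allocated to the test or control group".

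**The day's routine (Study design).** The pathway for patients randomised to control is the institute's usual one, "including procedure explanation and consent acquisition". After the explanation of the day, "the physician will ask the patient to read the informed consent and to sign it, if they agree". The patient then waits to be called. In the test arm, "the graphic novel will be provided to the patients after the initial colloquium", to be read during the wait.

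**Questionnaire timing (Assessing anxiety and Abstract).** The subsection opens with "After EUS-FNB, all the recruited patients will receive the Beck Anxiety Inventory (BAI" and adds the modified DASS-21. The Abstract also puts both questionnaires after the biopsy, in all enrolled patients. The second sentence of Assessing anxiety says the opposite: "Prior to the endoscopic procedures (i.e., EUS-FNB), these questionnaires will be administered anonymously".

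**The concern.** In the order described, a patient is already randomised when asked to sign the consent that forms part of the biopsy routine, and may decline. A patient may also change their mind while waiting, or the biopsy may not take place for some other reason. If the questionnaires come only after EUS-FNB, none of these patients has a point at which the outcome is measured.

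The analysed group would then be those who had the biopsy, a subset defined after randomisation. The comic depicts the procedure and the outcome is anxiety about it. Whether a frightened patient goes ahead could therefore depend on both the arm and the outcome. If the comic helped very anxious patients to go ahead, the test arm would keep high scorers that the control arm loses, and a benefit would be masked. If it put patients off, a benefit could appear where there is none.

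**Working it through.** The article gives no sample size, SD, target effect or rate of biopsies not done, so there is no figure of the plan's own to reproduce. The check is mainly one of sequence. The arithmetic only gives a sense of scale.

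**1. Order of events under Study design**

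| Step | Event | Relative to allocation |
|---|---|---|
| a | Lesion requires tissue acquisition; study consent signed | before |
| b | Random allocation | – |
| c | Colloquium, explanation, consent signed if the patient agrees | after |
| d | Comic handed over (test arm), waiting period | after |
| e | EUS-FNB | after |

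The form at step c is called only the informed consent. Study consent is already a condition of allocation, and the routine is said to include consent acquisition, so procedure consent is the natural reading. If it were the study consent, it would come after randomisation and conflict with the inclusion criterion. Either way the sequence needs correcting.

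**2. Is the patient exposed to the comic before the point of loss?** Consent follows the explanation, the patient then waits, and the comic is given after the colloquium for reading during the wait. The order of signature and comic is not stated outright, but signature first is likelier.
- Refusal at step c: probably before exposure. Loss should then be similar in the two arms, and the main cost is precision.
- Withdrawal at step d: after exposure. Loss could differ by arm.

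**3. What each timing statement implies for a randomised patient without a biopsy**

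| Statement | Timing | Outcome if no biopsy |
|---|---|---|
| Abstract | after EUS-FNB | no assessment point |
| Assessing anxiety, first sentence | after EUS-FNB | no assessment point |
| Assessing anxiety, second sentence | before EUS-FNB | not lost merely because the biopsy is not done |

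**4. Precision, on assumed inputs.** Take a standardised effect of 0.5, two-sided alpha 0.05, 80% power and 1:1 allocation. Then n = 2(1.96 + 0.84)²/0.5² ≈ 62.8, or 63 per arm. With a fraction d of scores lost equally in both arms, power is Φ(0.5·√(63(1 − d)/2) − 1.96), and 63/(1 − d) per arm must be randomised to keep 63 evaluable:

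| Loss d | Power | Randomised per arm to keep 63 |
|---|---|---|
| 2% | 79.3% | 65 |
| 5% | 78.1% | 67 |
| 10% | 75.9% | 70 |
| 15% | 73.5% | 75 |

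**5. Bias, on assumed inputs.** Let patients without a score lie D above those with one, and let the loss be d_T in the test arm and d_C in the control arm. Each full-arm mean is the observed mean plus d·D, so the observed test-minus-control difference departs from the full one by D(d_C − d_T).
- Loss 5% v 5%, any D: 0
- Loss 2% v 8%, D = 0.5 to 1.0 SD: 0.03 to 0.06 SD
- Loss 0% v 10%, D = 0.5 to 1.0 SD: 0.05 to 0.10 SD

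A deliberately harsh example in BAI points: 20 per arm, mean 15, and two control patients scoring 30 are lost with none lost in the test arm. The observed control mean is (20 × 15 − 2 × 30)/18 = 240/18 = 13.3, a shift of 1.7 points. This result comes from the one-sided loss and the extreme scores that were assumed. It is not an estimate for this trial.

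**The case against.** The strongest reply is that the second sentence of Assessing anxiety already puts the questionnaires before the biopsy. The stated aim in the Introduction, anxiety in patients waiting for a biopsy, fits that timing. On that reading a biopsy not done does not by itself remove the score. This is correct, and it makes the loss of outcome conditional. It does not remove the point, because the after-biopsy timing appears twice, once in the Abstract.

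A second reply is that the consent step most likely precedes the comic, so a refusal there cannot be a reaction to reading it. That also stands. Only withdrawal during the wait is open to an effect of the intervention.

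A third is that handling of randomised patients without a biopsy belongs in the full protocol or SAP. For analysis rules this is right, and their absence from an article is no defect. But the schedule of assessment is stated here, and no analysis plan can recover a score that the schedule never collects.

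A reader might go further and infer that eligibility itself hangs on a biopsy agreed or confirmed only after randomisation. The article does not support this. Eligibility rests on the indication for tissue acquisition and on study consent, both met before allocation. Neither procedure consent nor a completed biopsy is a criterion, and no later confirmation is described. Nor does it document that the most anxious patients decline most often, or that endoscopists will find nothing to biopsy.

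**Conclusion.** The point holds in a limited, conditional form. Allocation precedes what is most naturally the procedure consent, and the article contradicts itself on whether the questionnaires come before or after EUS-FNB. If they come after, randomised patients without a biopsy have no outcome, and the comparison is restricted to a group selected after randomisation.

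The size and direction of any bias cannot be determined from the document and may be small. It is nil if loss is equal in both arms and the missing patients differ from the rest to the same degree. It is 0.05–0.10 SD under an assumed 0% versus 10% loss. The loss of precision is modest: about 76% power instead of 80% at 10% loss, again on assumed inputs. Correction is worthwhile because the defect lies in the stated schedule and is nearly free to remove, not because serious bias has been shown.

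**What to change.** 1. Reconcile the timing statements in the Abstract and in Assessing anxiety. State that every randomised patient completes the BAI and mASS-14 at the end of the waiting period, before EUS-FNB and regardless of whether it is then performed, and is analysed in the allocated arm. This settles the contradiction and matches the aim of measuring anxiety during the wait.
2. In Study design, say which consent is meant at the routine step. Allocate only after both the study consent and the procedure consent are signed, and before the comic is handed over. Refusals at that step then occur before randomisation and cost no randomised patients.

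The cost is a wording change and a small shift in the moment of allocation. A few patients who do not go on to biopsy stay in the analysis, which suits a question about anxiety while waiting. Recording the reason for any biopsy not done, by arm, is a useful addition but not essential.
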